##### Muscular strength

2.6.2.6

Muscular strength is assessed using an estimated 1-RM from 10-RM of leg press and chest press (*Matrix Fitness, Cottage Grove, WI*). Additionally, 10-RM of chair squat, chest press, glute bridge, standing row, lunges, shoulder press (i.e., the exercises completed in the exercise intervention) using resistance bands (*Bodylastics USA, Boca Raton, FL*) and dumbbells are also completed to calculate weight intensity for exercise sessions. Participants perform 1 to 2 warm-up sets of 6 to 8 repetitions. The participant proceeds to complete sets of 10 repetitions with increasing weights in each set until volitional fatigue is reached on the 10th repetition. The weight of the participant’s 10-RM is recorded in kilograms and used to estimate 1-RM using validated equations (48, 49). Isometric handgrip strength is measured in the dominant upper limb (*Camry Digital Hand Dynamometer, El Monte, CA*). Participants perform 3 trials in a standing position with their arms down by their side, with the highest result used for analysis.

##### Psychosocial measures

2.6.2.7

Quality of life is assessed using the European Organization for Research and Treatment of Cancer questionnaires C-30 (50) for all patients, plus the cancer specific ones given to each participant based on diagnosis, prostate cancer-25 (51), colorectal cancer-29 (52), breast cancer-45 (53). Quality of life and physical function is assessed through the PROMIS-29 (54). Sleep quality is assessed via the Pittsburg Sleep Quality Index (55). Anxiety is assessed using the State Trait Anxiety Inventory (56). Common treatment-related toxicities is assessed via the patient reported outcome version of the Common Terminology Criteria for Adverse Events (57). Additionally, treatment symptoms are monitored via the therapy-related symptoms checklist completed at each supervised exercise session, and weekly phone call for the unsupervised group (58). Finally, patient views on exercise benefits, barriers, and preferences, as well as acceptability and feasibility of measures (59) are assessed in addition to their satisfaction with the intervention via an exit survey completed only at follow-up.

#### Covariates

2.6.3

##### Participant characteristics

2.6.3.1

Participant demographic and medical history data are collected at baseline with the administration of a study-tailored questionnaire. Changes in demographic and medical history data (e.g., medical conditions, medication, and cancer treatment) are monitored throughout the study period and confirmed at each testing time point.

##### Dietary intake

2.6.3.2

Recent dietary patterns are assessed using the automated self-administered 24-hour dietary assessment tool (60). Participants complete 3 assessments at home on 2 weekdays and 1 weekend day, recording all food and drinks consumed during the previous 24-hour period.

##### Physical activity logs

2.6.3.3

The AC and UNSUP groups complete a daily activity log throughout the 16-week intervention. During the supervised exercise sessions, the SUP group is asked about their physical activity completed outside the supervised sessions over the previous week. In addition, the SUP group completes daily activity logs during the follow-up period. In the activity logs, the participants are asked to record the type of exercise performed, time spent performing the exercise, intensity of the exercise bout (rate of perceived exertion [Borg scale 1-10]), and day of the week in which it was completed.

### Intervention adherence and acceptability

2.7

Exercise adherence will be assessed according to 1) the percentage and number of prescribed sessions performed and 2) the average minutes of exercise/week, collected from the Fitbit (61). Participant adherence will be captured by 1) percentage and number of prescribed sessions attended (participants must attend≥70% of sessions to be considered compliant with exercise program e.g.,≥34 sessions), and 2) average minutes of exercise/week (participant must complete≥70% of prescribed minutes) performed at the prescribed intensity (62, 63). Intervention acceptability and feasibility will be assessed via Acceptability of Intervention and Feasibility of Intervention questionnaires at month 4 (59). Items are measured on a 5-point Likert scale (completely disagree to completely agree), and the score is calculated mean. An average rating of 4 or higher will be considered feasible/acceptable.

### Follow-up

2.8

The planned duration of the exercise intervention is 16 weeks. However, to account for any unforeseen illness, family or medical emergency, or unplanned travel that might prevent participants from completing 48 exercise sessions within 16 weeks, all participants will have a total of 18 weeks to complete these sessions. Any sessions not completed within the 18-week period will not be made up and will be counted as a missed session. All patients will be followed for 4 months after the intervention is completed unless the patient withdraws consent. During this follow-up period, patients who are in the exercise interventions (SUP and UNSUP) will be encouraged to continue with exercise and will be provided an exercise prescription similar to the prescription provided during the exercise intervention, which will be calculated based on their post-exercise intervention assessment.

### Adverse events

2.9

Each patient is evaluated for potential adverse events (e.g., lymphedema, pain, muscle soreness, nausea, etc.) at each supervised testing visit and each exercise session, including the supervised sessions for the SUP intervention and telehealth calls for the UNSUP intervention. Participants are provided with a phone number to contact study staff to report potential intervention-related adverse events. Participants are assessed and graded according to the National Cancer Institute Common Terminology Criteria for Adverse Events (CTCAE) V5 (64) and will be documented by the study personnel at each testing or exercise session. Staff will report on study progress and injuries during weekly meetings either in person, by phone, or through weekly email updates. All adverse events, both serious and nonserious, and deaths that are encountered from initiation of study intervention, throughout the study, and within 30 days of the last study intervention sessions, should be followed to their resolution, or until the principal investigator assesses them as stable or determines the event to be irreversible, or the participant is lost to follow-up.

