#### Virtually supervised exercise intervention (SUP group)

2.5.1

Patients randomized to the SUP intervention participate in a home-based 16-week periodized aerobic and resistance exercise program performed three days per week, with each session lasting approximately 45-90 minutes based on the week in the training period. SUP exercise sessions are supervised by an exercise trainer through video conference technology (i.e., Zoom). The home-based intervention consists of a systematically progressed exercise program that starts at a low intensity and gradually increases to high intensity over the 16-week duration. Each session begins with a 5 min warm-up of low-intensity aerobic cycling on a stationary bike and concludes with 5 min of cooldown. Total-body resistance training is comprised of 6 resistance exercises performed using dumbbells and resistance bands, followed by the cycling aerobic exercise bout. Heart rate (HR) is monitored throughout aerobic exercise using a Fitbit heart rate monitor. One-repetition maximum (1RM) and maximal power output (wattage) obtained during baseline testing are used to determine resistance load for each resistance exercise and aerobic intensity, respectively. The details of a single exercise session of the SUP and UNSUP programs are further depicted in **Table 1**.

**Table 1 T1:** The THRIVE trial by intervention arm.

Intervention Arm	Supervised (SUP)	Unsupervised (UNSUP)	Attention Control (AC)
Oversight	Exercise trainer during each session via Zoom	Exercise trainer via weekly calls; sessions performed independently	Participants complete weekly records; stretching performed independently
Exercise frequency	3 sessions per week	3 sessions per week	3 sessions per week
Exercise intensity	Moderate-vigorous; monitored by maximal power output (wattage) and %RM	Moderate-vigorous; monitored by maximal power output (wattage) and %RM	Low intensity; low impact
Exercise time	45-90 min/session	45-90 min/session	10-15 min/session
Exercise type	Cycling & resistance exercise	Cycling & resistance exercise	Stretching

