**Figure 3 f3:**
[figure not shown]
Sample high intensity interval training (HIIT) workout. Dark blue bars indicate high intensity intervals at 90% maximal power output. Light blue bars indicate one-minute rest intervals at 10% maximal power output.

To increase compliance and aid in the standardization of the exercises, one-on-one supervision utilizing video chat (i.e., Zoom) with an exercise trainer occurs for each SUP exercise session. In addition, participants are asked to complete weekly records of physical activity performed outside the study. During each Zoom session, exercise trainers provide verbal encouragement, corrections to exercise technique, and modifications based on physical capabilities to mimic direct supervision in a clinic-based intervention. Wattage is monitored during each exercise session to ensure exercise intensity is achieved and maintained throughout each bout. Exercise equipment, including a stationary bike, resistance equipment, a Fitbit heart rate monitor, and a Wi-Fi enabled tablet, is delivered directly to each participant’s home in order to perform the intervention at home. Detailed written instructions on exercise equipment, connecting to video conferencing are provided and internet access is also provided for those who do not have access.

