#### Self-directed exercise intervention with regular guidance (UNSUP group)

2.5.2

Patients randomized to the UNSUP intervention participate in an unsupervised 16-week, telehealth-based, periodized aerobic and resistance exercise program performed three days per week using the same exercise prescription parameters as the SUP intervention (**Table 2**, **Figure 3**). Participants are provided with a stationary bike, resistance equipment, and a Fitbit heart rate monitor. HR is monitored during each exercise session using a Fitbit heart rate monitor to ensure exercise intensity is achieved and maintained throughout each bout. The exercise trainer calls each participant in the UNSUP intervention on a weekly basis to monitor progress and patients additionally complete physical activity logs. This training strategy will help to ensure that the intervention is implemented in the same way across all patients randomized to the UNSUP group. The phone calls are individualized as necessary to address individual problems to overcome barriers to success. Data on compliance and changes in physical activity reported by participants are captured and recorded electronically during the calls.

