### Measurements

2.6

Testing occurs at baseline (Week 0), post-intervention (Week 17), and follow-up (Week 33). All measures are completed at baseline, post-intervention, and follow-up unless otherwise specified below. A complete data collection schedule is provided in **Table 3**.

**Table 3 T3:** Timeline of the study visits of the THRIVE Trial.

Timepoints	Eligibility Screening	Baseline Testing	Intervention	Post-Intervention Testing	Follow-up Testing
	t_0_	t_1_ Week 0	Weeks 1-16	t_2_ Week 17	t_3_ Week 33
Assessments					
Medical History	✓				
Pregnancy Test (if applicable)	✓				
Physical Activity Level		✓		✓	✓
Blood Biomarkers		✓		✓	✓
Brachial and Non-invasive Aortic Blood Pressure		✓		✓	✓
Anthropometrics		✓		✓	✓
Muscular Strength		✓		✓	✓
Cardiopulmonary Fitness		✓		✓	✓
Physical Function		✓		✓	✓
Patient-Reported Outcomes		✓		✓	✓
Dietary Recall		✓		✓	✓
Exercise or Stretching Intervention			✓		
Assessment of Adverse Events, Toxicities, or Exercise Complications			✓		
Exit Survey					✓

Arrow denotes study visits.

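### In Weeks 1-16 adverse events and symptoms are actively elicited at up to 48 sessions in SUP and 16 calls in UNSUP, with no active route described for AC, so by-arm counts from these contacts carry detection bias

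*Protocol article*

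**What the plan says.** Only the protocol article is at hand. It ties active collection of adverse events and symptoms to the contacts through which each arm's programme is delivered.

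- **Adverse events (section 2.9).** Every patient is evaluated at testing visits and at exercise sessions, "including the supervised sessions for the SUP intervention and telehealth calls for the UNSUP intervention". All participants also get a phone number for reporting events that may be related to the intervention.
- **Symptom checklist (section 2.6.2.7).** The text reads: "treatment symptoms are monitored via the therapy-related symptoms checklist completed at each supervised exercise session, and weekly phone call for the unsupervised group". AC is not mentioned.
- **SUP contacts (section 2.5.1).** "one-on-one supervision utilizing video chat (i.e., Zoom) with an exercise trainer occurs for each SUP exercise session".
- **UNSUP contacts (section 2.5.2).** "The exercise trainer calls each participant in the UNSUP intervention on a weekly basis to monitor progress".
- **AC contacts.** Table 1 describes oversight as: "Participants complete weekly records; stretching performed independently". Section 2.5.3 adds that a trainer teaches the stretches at baseline and that the weekly records cover stretching compliance. Section 2.6.3.3 gives AC a daily activity log of exercise type, duration, intensity and day. No symptom or adverse-event item is described in either record.
- **Common to all arms.** Section 2.6 places all measures at Weeks 0, 17 and 33 unless stated otherwise. This covers the PRO-CTCAE of section 2.6.2.7.
- **Table 3.** The row "Assessment of Adverse Events, Toxicities, or Exercise Complications" is ticked only in the Weeks 1-16 column, without distinction by arm.

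**The concern.** All patients are starting or receiving chemotherapy, so symptoms and adverse events are to be expected in every arm whatever the exercise allocation. If one arm is asked three times a week, another once a week, and the third not at all until Week 17, the recorded counts will differ even when the true rates are the same. The error runs in one direction: the exercise arms look worse than AC.

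Two things are at stake. First, the Discussion cites the potential of exercise to reduce chemotherapy toxicity. A real reduction could be hidden, or an apparent excess created, in any by-arm table of events picked up at sessions or calls. Since the results are meant to inform larger trials, a distorted safety profile would be carried forward. Second, safety information on AC patients during the 16 weeks is thinner than on the others, although section 2.9 speaks of evaluating each patient.

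**Working it through.** **1. Contact counts.** Inputs: "home-based 16-week periodized aerobic and resistance exercise program performed three days per week, with each session lasting approximately 45-90 minutes" (section 2.5.1), and one UNSUP call per week (section 2.5.2).

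- SUP: 3 sessions/week × 16 weeks = 48. This reproduces the plan's own figure in section 2.8, "completing 48 exercise sessions within 16 weeks".
- As a further check, section 2.7 sets compliance at 70% of sessions: 0.70 × 48 = 33.6, rounded up to 34, as stated there. A SUP patient who is only just compliant still has 34 contacts.
- UNSUP: 1 call/week × 16 weeks = 16.
- AC: no call, session or adverse-event query described = 0.

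Adding the Week 17 testing visit, which all arms share, gives 49, 17 and 1.

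**2. What unequal contact could do to the counts.** The documents give no event durations or recall periods, so this step is an illustration. Assumptions:

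- the true event process is the same in all arms, with onset uniform over 112 days (16 × 7);
- an event is found only if the next contact falls within D days of onset, where D is duration plus recall;
- all contacts take place: SUP on days 0, 2 and 4 of each week, UNSUP on day 2 of each week, and the Week 17 visit on day 115 for everyone;
- the phone line is ignored.

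The share detected is the number of onset days that lie within D days before a contact, divided by 112.

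- **AC** (day 115 only): (D − 3)/112, or 0 if D ≤ 3. D = 7 gives 4/112 = 0.04; D = 14 gives 11/112 = 0.10; D = 28 gives 25/112 = 0.22.
- **UNSUP** (days 2, 9, …, 107, then 115): D = 2 gives 16 × 2 = 32, and 32/112 = 0.29. D = 3 gives 2 + 15 × 3 = 47, and 47/112 = 0.42. D = 7 gives 2 + 15 × 7 + 4 = 111, and 111/112 = 0.99.
- **SUP** (gaps of 2, 2 and 3 days; last session on day 109, then day 115): D = 2 gives 15 × 6 + 4 = 94, and 94/112 = 0.84. D = 3 gives 15 × 7 + 4 = 109, and 109/112 = 0.97. D = 7 gives 112/112 = 1.00.

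| Assumed D (days) | SUP | UNSUP | AC |
|---|---|---|---|
| 2 | 0.84 | 0.29 | 0.00 |
| 3 | 0.97 | 0.42 | 0.00 |
| 7 | 1.00 | 0.99 | 0.04 |
| 14 | 1.00 | 1.00 | 0.10 |
| 28 | 1.00 | 1.00 | 0.22 |

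AC is lowest at every window from 2 to 28 days. The SUP-UNSUP gap is large only at 2-3 days and has practically closed at 7.

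**3. Table 3 against section 2.9.** Section 2.9 has adverse events evaluated at each testing visit and covers events up to 30 days after the last session. Table 3 leaves the Week 17 and Week 33 columns unticked. The two do not agree.

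**The case against.** Several points on the other side stand.

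- **AC is not unobserved.** A reader might infer from the contact counts that AC events are missed altogether. The text does not support that: section 2.9 covers every patient at the testing visits, so AC is evaluated at Weeks 17 and 33, and AC patients have the phone line. What remains is under-detection, chiefly of brief or mild events. The phone line helps only in part, because it is offered for events that may be related to the intervention. An AC patient has little reason to link chemotherapy nausea to stretching.
- **Not every toxicity comparison is affected.** A reader might also infer that all toxicity data are biased. PRO-CTCAE is given at Weeks 0, 17 and 33 in all arms, so contact frequency does not enter into it. The same holds for the schedule of the testing-visit evaluations.
- **Counts need not scale with contacts.** The 3:1 ratio of SUP to UNSUP contacts does not imply three times as many recorded events. A patient asked weekly can recall much of the week.
- **No formal between-arm test of adverse events is stated,** and no checklist endpoint is defined. The bias is therefore conditional on a by-arm tabulation being made. Such a table is a natural product of a safety section, and the checklist sits under secondary outcomes. The condition is likely to be met, but it is a condition.
- **The article is condensed.** The word introducing the SUP and UNSUP contacts in section 2.9 need not be exhaustive, and the AC forms cannot be seen. Against this, the article goes through contacts arm by arm in Table 1 and in sections 2.6.2.7 and 2.9, and none of these gives AC an active route. AC stretching sessions have no staff present to document anything.

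**Conclusion.** The concern holds in a bounded form. As described, active elicitation of adverse events and checklist symptoms in Weeks 1-16 is up to 48 : 16 : 0 for SUP, UNSUP and AC. Any by-arm table of session- or call-elicited events is open to detection bias against the exercise arms. For the checklist, no AC data are described at all. The bias is mainly a matter of exercise versus AC; between SUP and UNSUP it matters only for events that are both brief and not recalled at the weekly call.

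The contact counts come from the text. The detection shares rest on the assumed windows and contact days, and show direction and rough size only. The conclusion also assumes that the full protocol's AC forms carry no adverse-event or symptom items beyond what the article describes. The primary accelerometry comparison and PRO-CTCAE are not touched. The Table 3 mismatch is a minor point of reconciliation.

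**What to change.** 1. Put the same short adverse-event and symptom items on a weekly form in all three arms, completed in the same way in each. For AC, add it to the weekly record already returned.
2. Base between-arm comparisons of events and symptoms on that form, the common testing visits and PRO-CTCAE.
3. Report the additional events elicited at SUP sessions descriptively, within arm, and say in the table note that contact frequency differed.
4. If AC is in fact queried weekly under the full protocol, say so in sections 2.5.3, 2.6.2.7 and 2.9.
5. Reconcile the adverse-event row of Table 3 with section 2.9.

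The cost is one short weekly page per patient, its review by existing staff, and a protocol clarification. If the form cannot be added, restricting between-arm comparison to the testing visits and PRO-CTCAE adds no data collection, but it leaves the thinner information on AC between baseline and Week 17 as it is.

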### Data monitoring and management

2.10

Data monitoring begins at the time of participant registration and will continue until protocol completion. While the study team collects, manages, and performs quality checks of the data, the principal investigator or their designated representatives may also perform quality assurance checks as needed. All data are stored on a secure network drive using REDCap (Research Electronic Data Capture; Vanderbilt University) (35, 65), a Health Insurance Portability and Accountability Act–compliant web-based application hosted by Partners HealthCare Research Computing, Enterprise Research Infrastructure & Services, on password-protected computers, with hard-copy data stored in locked filing cabinets in card-access facilities. The results of this study will be presented in publication, conference, and invited speaker formats.

### Sample size

2.11

In order to assess change from baseline to post-intervention in daily exercise minutes for the SUP intervention versus AC; and the UNSUP intervention vs. AC, we anticipate to enroll a total of 45 patients with breast, prostate, or colorectal cancers, who will be randomized to SUP (n=15) or UNSUP (n=15) exercise groups, or AC (n=15). Based on data from a recent study led by Lee et al. (2019) examining how a HIIT intervention was feasible for breast cancer patients undergoing chemotherapy, we assume the average weekly minutes of moderate-to-vigorous physical activity to be 30 minutes for all participants at baseline, 60 minutes for the SUP and UNSUP exercise groups and 45 minutes for the AC during 4-month post-intervention, with standard deviation of 12. To detect such difference in the pre-post change in mean minutes of exercise per week (corresponding to a standardized effect size of 1.25), comparing supervised and unsupervised exercise groups to control group using t-test, with two-sided α = 0.05, a sample size of 12 subjects in each group is needed in order to achieve 80% power. Assuming 80% drop off between baseline and post-intervention (Week 17-19), a sample size of 15 patients each group is needed to be randomized.

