#### Primary outcomes

2.6.1

Minutes of moderate-to-vigorous physical activity are utilized as the primary outcome variable and assessed via the ActiGraph wGT3X-BT (*ActiGraph, Pensacola, FL*), which is worn by patients for seven days at all times except for water activities and sleeping. Other measures of physical activity such as sedentary time, light physical activity, step count etc. are also captured using the ActiGraph. Additionally, the 7-day Physical Activity Recall interview is conducted over the phone asking participants to recall their exercise for the same 7 days that the ActiGraph was worn. Only wake wear time is utilized, and participants must have recorded a minimum of four days with at least 600 minutes of wake wear time per day for inclusion in the analysis. Non-wear time is excluded from the analysis, defined as≥90minutes of consecutive zeros with a 2-minute spike tolerance (39). Commonly used cutoff points among cancer patients will be used to classify sedentary time (<100 counts per minute), light physical activity (100–1951 counts per minute), and moderate-to-vigorous physical activity (≥1952 counts per minute) (40, 41).

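### The sample-size section assumes 80% drop-off, but 12 evaluable patients per group inflate to the stated 15 only under 20% drop-off

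*Protocol article*

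**What the plan says.** The Sample size section (2.11) compares each exercise group with the attention control on the change in weekly minutes of moderate-to-vigorous activity. It assumes 30 minutes at baseline in every group, then "60 minutes for the SUP and UNSUP exercise groups and 45 minutes for the AC during 4-month post-intervention", "with standard deviation of 12". It describes the resulting difference as "corresponding to a standardized effect size of 1.25". The test is specified "using t-test, with two-sided α = 0.05", and the conclusion is that "a sample size of 12 subjects in each group is needed in order to achieve 80% power".

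The next sentence turns this evaluable number into the number to randomize: "Assuming 80% drop off between baseline and post-intervention (Week 17-19), a sample size of 15 patients each group is needed". The total of 45 appears consistently in the abstract, in Study design (2.1) and in Sample size (2.11). No other section gives a drop-out or retention assumption for this trial. The percentages in Intervention adherence and acceptability (2.7) concern sessions and minutes completed, and those in the Discussion are session adherence in other studies.

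**The concern.** The attrition rate is the only step between the 12 patients per group that the power calculation requires and the 15 that are randomized. If the rate is wrong as printed, the published justification for 45 patients does not follow from its own inputs, and a reader cannot reconstruct it without guessing what was meant. The article also says that the trial should inform the design of larger ones, so an attrition assumption taken from it could be carried into later calculations.

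**Working it through.** **Inputs, all from Sample size (2.11).** Baseline mean 30 in all groups; post-intervention means 60 (exercise) and 45 (control); SD 12; two-sided α = 0.05; t-test; target power 80%; 12 evaluable and 15 randomized per group; drop-off 80% as written. The SD of 12 is taken as the SD of the change, because that is what an effect size of 1.25 implies.

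**Step 1: effect size.** Difference in change = (60 − 30) − (45 − 30) = 15. Standardized: 15/12 = 1.25. This matches the plan.

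**Step 2: evaluable number per group.** Two-sample t-test with the noncentral t distribution, 2n − 2 degrees of freedom and noncentrality 1.25 × √(n/2). Solving for 80% power gives n = 11.09, rounded up to 12.

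| Evaluable per group | Power |
|---|---|
| 11 | 79.6% |
| 12 | 83.3% |
| 15 | 91.0% |

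The plan's 12 reproduces. (The normal approximation would give 11.)

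**Step 3: inflation for attrition.** Number to randomize = evaluable number / (1 − drop-off).

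| Drop-off | To randomize for 12 evaluable | Evaluable out of 15 |
|---|---|---|
| 80% (as written) | 12/0.20 = 60 per group, 180 in total | 15 × 0.20 = 3 |
| 20% | 12/0.80 = 15 per group, 45 in total | 15 × 0.80 = 12 |

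The cruder inflation, n × (1 + drop-off), does not rescue the 80% either: 12 × 1.8 = 21.6, rounded up to 22.

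**Step 4: what the literal wording would imply.** With 3 per group, noncentrality is 1.25 × √1.5 = 1.53 on 4 degrees of freedom, and two-sided power is 22.0%. A simulation with 400,000 replicates also gave 22.0%. The normal approximation gives 33.4%, but it is not suitable at this size.

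Step 3 does not depend on the effect size, the SD or the test. It uses only the plan's own 12, 15 and 80%.

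**The case against.** The strongest reply is that this is visibly a slip of wording. Twelve divided by 0.80 is exactly 15, the total of 45 is the same wherever it appears, and the correction changes no test, endpoint, allocation or number of patients. Statistical analysis (2.12) also describes the testing as exploratory. All of this stands, and it limits the point to an error in the stated justification. It does not remove the error: the printed rate is incompatible with the printed numbers, and nothing elsewhere in the article corrects it.

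A reader might infer more, and three such readings are not supported.

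- **That the trial has 22% power, or was planned for 3 evaluable patients per group.** This follows only if the 80% is taken literally against the evidence of the 12 and the 15. The plan attaches its 80% power to 12 per group, and that claim is correct. What the printed rate contradicts is the step to 15.
- **That retention would be monitored against this figure, so that a very large loss would pass as planned.** Data monitoring and management (2.10) covers data collection, quality checks and storage. It sets no retention target and does not refer to the attrition assumption.
- **That the allowance is also too small because of the accelerometer wear rule.** Primary outcomes (2.6.1) does say that "participants must have recorded a minimum of four days with at least 600 minutes of wake wear time per day for inclusion in the analysis". But the article gives no rate of invalid wear, and it does not define drop-off so as to exclude patients without usable data. How many patients the rule would remove beyond the allowance cannot be derived from the document.

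**Conclusion.** The concern holds as an internal inconsistency in the Sample size section. With 12 evaluable and 15 randomized per group, the drop-off must be 20%; the stated 80% would require 60 per group, four times the planned number. The likely explanation is that retention was meant. That is an inference from the arithmetic, which the sponsor should confirm.

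On that reading the design is intact: 12 evaluable per group give 83.3% power for a standardized difference of 1.25, with SD 12 as the SD of the change and the protocol's unadjusted two-sided t-test for each comparison with control. The 22% belongs only to the literal wording and should not be cited as the trial's power.

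**What to change.** The sponsor should confirm the intended assumption. If it was 80% retention, replace the opening of the sentence with: assuming 20% drop-off (80% retention) between baseline and post-intervention. Showing the step 12/0.80 = 15 beside it would prevent a repeat. Keep 12 evaluable and 15 randomized per group, 45 in total.

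The cost is one sentence, with no additional patients and no change to the analysis. If the sponsor had some other rate in mind, the number to randomize would have to be recalculated as 12/(1 − rate).
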